# Association between changes in cerebral grey matter volume and postoperative cognitive dysfunction in elderly patients: study protocol for a prospective observational cohort study

**DOI:** 10.1186/s12871-016-0285-z

**Published:** 2016-11-25

**Keywords:** Postoperative cognitive dysfunction, Long-term outcomes, Surgery, Anesthesia, Cerebral volume

## Abstract

**Background:**

Cognitive decline is frequently observed in elderly patients after major surgery. The pathophysiology of postoperative cognitive dysfunction (POCD) remains unclear. The aim of our investigation is to identify potential associations between brain volume change and POCD in elderly patients undergoing major surgery.

**Methods:**

This is a prospective observational cohort study approved by the regional ethics board. We intend to compare specific brain volumes (hippocampus, lateral ventricle, total grey matter volume, regional cortical thickness) on magnetic resonance imaging and cognitive functions determined by a neuropsychological assessment battery in 70 study participants aged ≥65 years before and 3 and 12 months after major noncardiac surgery. Thirty volunteers will be included as matched nonsurgical controls. The primary endpoint of the study is the change in hippocampal volume over time in patients with and without POCD. The secondary endpoint is the correlation between the change in cerebral volume and cognitive function. We will follow the STROBE guidelines for reporting the results of observational studies.

**Discussion:**

We hypothesize that surgery under general anesthesia is associated with a loss of cerebral grey matter, and that the degree of postoperative cognitive dysfunction correlates with the extent of atrophy in areas of the brain that are relevant for cognitive functions. The validation of reproducible anatomical biomarkers, such as the specific brain volumes examined in our cohort, may serve to evaluate the effect of preventive strategies and treatment interventions for POCD in follow-up studies.

**Trial registration:**

Clinicaltrials.gov NCT02045004. Registered 22 January 2014. Kofam.ch SNCTP000001751. Registered 21 April 2016 (retrospectively registered).

## Background

Anesthesia care for patients in their seventies or eighties has an ever-growing presence in clinical practice given the demographic development in many industrialized countries. Variable degrees of cognitive decline are frequently observed after major surgery in elderly patients and have been defined as postoperative cognitive dysfunction (POCD) [1]. Clinical studies have reported an incidence of POCD of up to 41% in surgical patients older than 60 years (Table 1) [2]. In many patients, this is a transient problem. But in some patients, cognitive deficits are long-term or permanent [1, 2]. POCD may also develop in younger patients [3] and after minor surgery [4]. The occurrence of POCD is associated with increased mortality and important socioeconomic consequences [5].

**Table 1 Tab1:** Incidence of POCD after noncardiac surgery

Study	Population	Time for postoperative test	POCD rate (%)
Moller et al. [1]	Patients ≥60 undergoing major abdominal, thoracic, or orthopedic surgery	1 week and 3 months	25.8 and 9.9%, respectively
Monk et al. [2]	Patients >60 undergoing minimally invasive, intraabdominal/thoracic, or orthopedic surgery	1 week and 3 months	41.4 and 12.7%, respectively
Johnson et al. [3]	Patients 40–60 undergoing major abdominal or orthopedic surgery	1 week and 3 months	19.2 and 6.2%, respectively
Canet et al. [4]	Patients >60 undergoing minor surgery	1 week and 3 months	6.8 and 6.6%, respectively

*POCD* postoperative cognitive dysfunction

The potential association between exposure to anesthesia and the development of dementia in elderly patients remains a controversial topic [6, 7]. So far, a direct association between surgery and long-term cognitive decline has not been established [8]. The pathophysiology of POCD is poorly understood, and no preventive strategy or treatment has been described so far [9]. A retrospective analysis of cohort data suggests that surgery may be associated with a decrease in brain volume [10]; however, no analysis of a potential link between cerebral atrophy and cognitive functions was made. We would like to reproduce and verify these results and investigate a possible relationship with the postoperative cognitive performance in surgical patients.

The principal objective of this observational cohort study is to prospectively test the hypothesis whether major noncardiac surgery under sevoflurane-based general anesthesia is associated with a loss of cerebral grey matter in elderly patients. We also hypothesize that the degree of POCD correlates with the loss of grey matter in brain areas relevant for cognitive functions.

## Methods

### Study design and setting

This prospective, observational cohort study is being conducted at the University Hospital Basel, Switzerland. Study recruitment commenced in July 2015 and is expected to last for 36 months. The regional ethics committee (EC) approved the study prior to participant inclusion (Ethikkommission Nordwestschweiz, protocol: EKNZ 2014–155, 1 August 2014). The study was registered on clinicaltrials.gov (NCT02045004) on 22 January 2014 and on Kofam.ch (SNCTP000001751) on 21 April 2016.

### Study population

Two groups of study participants will be investigated in this prospective cohort study. Seventy patients aged ≥65 years undergoing major surgical procedures will be recruited for this study (Group 1). Thirty volunteers aged ≥65 years will be recruited as matched nonsurgical controls (Group 2).

#### Recruitment and informed consent

Study participants in the surgical group (Group 1) will be recruited as patients of the University Hospital Basel, Switzerland. Eligible patients are identified by screening the daily list of visits in the preoperative anesthesia clinic. They are either contacted personally on the same day, or by mail in a letter including participant information and a consent form. A follow-up phone call by an investigator will provide further information about relevant details of the study. Study participants in the nonsurgical control group (Group 2) will be recruited from an existing study subject registry established by the Memory Clinic at the Felix Platter Hospital, Basel, Switzerland. Nonsurgical controls are matched to surgical patients according to age, gender and level of education.

The study is conducted with written informed consent from all study subjects and is conducted with respect of the most recent version of the Declaration of Helsinki [11]. Participants are informed that participation in the study is voluntary, and that they are free to withdraw at any time. Recruitment and consenting of study participants by members of the research team is in-line with Good Clinical Practice (GCP) [12].

#### Inclusion and exclusion criteria

Study inclusion and exclusion criteria appear in Table 2. All patients aged 65 years or older, American Society of Anesthesiologists’ physical status I–III, who are scheduled from major elective surgery under general anesthesia at the University Hospital Basel, are eligible for study inclusion in Group 1. Further inclusion criteria comprise a home location suitable for testing, German as their first language, and an Instrumental Activities of Daily Living [13] score ≥6. Participants in Group 2 are volunteers who present equal inclusion and exclusion criteria, without planned surgery.

**Table 2 Tab2:** Study inclusion and exclusion criteria

Criterion	Screening procedure
Inclusion criteria	
Age ≥65 years	Medical record
Home location suitable for testing	Medical record
German as a first language	Medical record or recruitment telephone call
IADL score ≥6	Baseline assessment
ASA physical status I–III	Baseline assessment
Major elective surgery^a^	Medical record
Planned general anesthesia^a^	Baseline assessment
Exclusion criteria	
Cardiac surgery^a^	Medical record
Neurosurgery including carotid endarterectomy, or any type of surgery precluding postoperative testing^a^	Medical record
(Another) major surgery within the study timeline	Medical record, recruitment telephone call or baseline interview
General anesthesia up to 3 months prior to inclusion	Medical record
Baseline MMSE score <24	Baseline neuropsychological assessment
Dementia criteria per DSM-5	Baseline neuropsychological assessment
Previous pathological cerebral imaging (if available)	Medical record
History of cerebral or cerebrovascular pathology, head trauma, neurodegenerative illness or epilepsy	Medical record
Chronic use of psychiatric medication	Medical record or baseline interview
Alcohol or substance abuse	Medical record or baseline interview
History of chronic pain unrelated to the planned surgery	Medical record
Chronic medical illness known to induce encephalopathy	Medical record
Any contraindication for MRI (e.g., pacemakers and other MRI-incompatible implantable device)	Medical record, recruitment telephone call or baseline interview
Claustrophobia	Medical record, recruitment telephone call or baseline interview
Incidentally diagnosed disease or unfavorable course of disease in participants who choose not to be informed	Any study assessment
Lack of informed consent	Recruitment telephone call

*ASA* American Society of Anesthesiologists, *DSM-5* Diagnostic and Statistical Manual of Mental Disorders, Fifth Edition, *IADL* Instrumental Activities of Daily Living, *MMSE* Mini-Mental State Examination

^a^Not applicable for the nonsurgical control group

### Outcomes

The primary endpoint of this study is the degree of change in hippocampal volume over time between patients with and patients without POCD. Other specific cerebral volumes measured are the lateral ventricles, the total grey matter volume, and regional cortical thickness. The secondary endpoint is the correlation between the change in cerebral volume and the change in cognitive function.

### Study procedures

Study-related procedures include a baseline multimodal assessment, intraoperative data acquisition and postoperative multimodal assessments on study visits scheduled 1 week, 3 months and 1 year after surgery. Figure 1 shows the flow diagram for the study assessments on a time line.

**Fig. 1 Fig1:**
[figure not shown]
Flow diagram of study procedures

#### Anesthetic management

Anesthesia will be standardized. Intravenous propofol and fentanyl will be used for induction of general anesthesia, atracurium or rocuronium for neuromuscular blockade. Patients will be intubated and mechanically ventilated with an air/oxygen mixture to maintain an end-tidal carbon dioxide at 4.6 ± 0.6 kPa. Inhalational sevoflurane, intravenous fentanyl or remifentanil will be used to maintain anesthesia. Intraoperatively, the dose of anesthetics will be controlled using depth of anesthesia monitoring at a targeted bispectral index (BIS) of 40–60 and end-tidal sevoflurane concentration monitoring. Data will be downloaded directly from the patient monitor (IntelliVue™ MX800, Philips Healthcare, Zurich, Switzerland) and the anesthesia machine (Perseus™, Dräger, Liebefeld, Switzerland) on a personal computer using ICM+ software (Cambridge Enterprise Ltd, University of Cambridge, United Kingdom).

#### Neuropsychological assessment

The Consortium to Establish a Registry for Alzheimer’s Disease-Neuropsychological Assessment Battery (CERAD-NAB) [14], Trail Making Tests A and B [15], and phonemic fluency (s-words) [16] will be performed preoperatively, at 7 days, 3 months and 1 year postoperatively. Training of all study personnel and supervision of cognitive testing will be carried out by the Memory Clinic at Felix Platter Hospital. Cognitive functions will be quantified using the CERAD-NAB total score [17], in its demographically-corrected form [18]. A correction for short-term practice effects will be carried out based on previous work [19]. Table 3 shows the neuropsychological subtests used in this study [20]. The 15 variables resulting from neuropsychological assessment are converted into standard scores (z-scores) based on a normative sample [21], and the z-score changes from baseline are calculated. POCD is diagnosed if the decline is >1.0 standard scores in two or more of the 15 variables based on the diagnostic guideline for mild cognitive impairment and dementia related to Alzheimer’s disease by the National Institute on Aging-Alzheimer’s Association [22] and the American Psychiatric Association’s Diagnostic and Statistical Manual of Mental Disorders (DSM-5) [23]. Postoperative delirium is assessed using the Delirium Observation Screening scale [24] and, if applicable, the Confusion Assessment Method [25], administered 3 times daily until the fifth postoperative day.

**Table 3 Tab3:** Subtests of the neuropsychological assessment battery used for diagnosis of POCD

Test variable	Test description	Domain tested
CERAD-NAB word list-encoding	Total number of correctly learned words across three learning trials (number of words per trial = 10)	Verbal episodic learning
CERAD-NAB word list-delayed free recall	Total number of correctly remembered words after a delay following encoding	Verbal episodic memory
CERAD-NAB word list-savings	Proportion of correctly recalled words during delayed free recall relative to words learned in learning trial 3	Verbal episodic memory
CERAD-NAB word list-discriminability	Rate of correctly recognized words from encoding	Verbal episodic memory
CERAD-NAB word list-intrusion errors	Total number of intrusions committed during word list-encoding and -delayed free recall	Executive functions
CERAD-NAB figures-copy	Copy of four figures (circle, diamond, overlapping rectangles, cube)	Visuospatial ability
CERAD-NAB figures-delayed recall	Number of correctly reproduced figures from figures-copy following a delay	Visual memory
CERAD-NAB figures-savings	Proportion correctly reproduced figures at figures-delayed recall relative to figures-copy	Visual memory
Semantic fluency-animals	Number of animals produced within 1 min	Semantic memory
Boston naming test (15-items)	Number of spontaneously correctly named black and white line drawings (maximum = 15)	Language
Trail making test A	Time required to connect circles numbered from 1 to 25 in ascending order	Psychomotor speed
Trail making test B	Time required to connect circles containing numbers (1–13) and letters (A-L) in ascending and alternating order	Executive functions
Phonemic fluency	Number of words starting with the letter S produced within 1 min	Executive functions

*CERAD-NAB* Consortium to Establish a Registry for Alzheimer’s Disease-Neuropsychological Assessment Battery. Adapted from Mistridis et al. [20]

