#### Magnetic resonance imaging

Cerebral MRI will be performed at baseline, at 3 months, and 1 year postoperatively on the same day as the neuropsychological assessment. MRI analysis will be carried out by the Division of Neuroradiology at the University Hospital Basel. High-resolution anatomic and diffusion cerebral MRI will be performed using the hospital’s 3-Tesla MAGNETOM Prisma™ MRI scanner (Siemens, Zurich, Switzerland). For MRI analysis, we will assume that the same regions as those described in mild cognitive impairment and Alzheimer’s disease [29] are relevant to POCD. We will perform a region of interest (ROI) analysis (hippocampus, lateral ventricle, total grey matter volume, regional cortical thickness). Cortical reconstruction and volumetric segmentation will be performed with the FreeSurfer software suite [30], which is freely available for download online (http://surfer.nmr.mgh.harvard.edu).

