#### Statistical analysis plan

The quantitative imaging results will be correlated to the CERAD-NAB total score performance obtained on the same day as the MRI scans. The relationship of changes in volume with intraoperative depth of anesthesia (BIS) and the administered dose of sevoflurane expressed as age-corrected minimum alveolar concentration (MAC) equivalent [32] multiplied by time of administration will be calculated. We will use voxel-wise, multivariate analysis of variance (ANOVA) and the classification/prediction procedure on multi-parameter MRI data in order to build optimal composite predictors of patients’ neuropsychological outcomes. All statistical analyses will be performed using SPSS Statistics software, version 22 (IBM, Inc., Zurich, Switzerland). All graphs will be plotted using Prism, version 6 (GraphPad Software, Inc., La Jolla, CA, USA). An interim analysis will be performed to assess quality of data after primary data acquisition from 20 participants. We will follow the Strengthening the Reporting of Observational studies in Epidemiology (STROBE) statement [33] for all future reports related to this study.

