### Methodological considerations

#### Choice of study collective

Although POCD was described in middle-aged patients [3], the disorder has its highest incidence among patients over the age of 65 years. As most research on POCD was done in this age group, we decided to set the cut-off for participant age at 65 years. We excluded subjects with conditions known to induce changes in cerebral anatomy such as Alzheimer’s disease and other forms of dementia, a history of severe neurological disease, or chronic pain in order to obtain a patient sample free of pre-existing cognitive disorders that might confound the relationship between brain volumes and POCD. The addition of a group of nonsurgical participants serves to control for practice effects related to neuropsychological assessment, to observe the physiological cerebral atrophy rates in volunteers matched to the surgical group, and to establish a paradigm for further research on POCD.

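### The score's demographic correction should not be relied on as age control for the secondary change-versus-change correlation, and the analysis text should state that changes are analysed, adjusted for age, sex and education

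*Protocol article*

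**What the plan says.** The Outcomes section defines the secondary endpoint on changes: "The secondary endpoint is the correlation between the change in cerebral volume and the change in cognitive function". The Statistical analysis plan section describes the matching analysis differently: "The quantitative imaging results will be correlated to the CERAD-NAB total score performance obtained on the same day as the MRI scans". It does not say whether levels or changes enter, and it names no covariate for this correlation.

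The cognitive measure is fixed under Neuropsychological assessment: "Cognitive functions will be quantified using the CERAD-NAB total score [17], in its demographically-corrected form [18". The form of the correction is left to a cited source. The imaging side, under Magnetic resonance imaging, reads "We will perform a region of interest (ROI) analysis (hippocampus, lateral ventricle, total grey matter volume, regional cortical thickness", with no age or head-size correction stated.

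Demographics are handled in two other places. Under Recruitment and informed consent, "Nonsurgical controls are matched to surgical patients according to age, gender and level of education". For the diagnosis of POCD, the test variables are "converted into standard scores (z-scores) based on a normative sample [21], and the z-score changes from baseline are calculated"; whether those norms are age-specific is not stated. The Study population section sets a lower age limit only: "Seventy patients aged ≥65 years undergoing major surgical procedures will be recruited for this study (Group 1". Under Choice of study collective, one purpose of the control group is "to observe the physiological cerebral atrophy rates in volunteers matched to the surgical group", so the authors recognise atrophy unrelated to surgery.

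**The concern.** Older patients may plausibly lose both more brain volume and more cognitive performance over a year. If so, the two changes will correlate within the cohort even when neither is related to the other. A demographically corrected score invites the assumption that this has been dealt with. Such a correction is built to make score levels comparable between people of different age, sex and education. When the same person's score is subtracted from itself across visits, most or all of the correction goes with it.

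At stake is the reading of the secondary result. An association that runs through age could be reported as a link between atrophy and cognitive decline after surgery. The mismatch between a change endpoint and an analysis sentence that can be read as levels makes this worse, because the correction behaves differently in the two cases.

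**Working it through.** **The plan's own figure.** The documents give no sample size or power for the secondary correlation. The evaluable number comes from the primary endpoint: difference 0.4 cm³, SD 0.45, POCD incidence 41%, two-sided 5%, power 90%. Total = [0.45 × (1.960 + 1.282) / 0.4]² / (0.41 × 0.59) = 54.98. Rounding up by group gives 33 + 23 = 56, and 56 / 0.80 = 70. Both stated numbers reproduce (power at 56 is 90.5% by the normal approximation and 89.5% by the noncentral t). I use n = 56 below, with n = 70 for no loss to follow-up.

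**Does the correction survive differencing?** Let T0 and T1 be the raw scores and f the amount set by demographics.

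- Additive, demographics held at baseline: (T1 − f) − (T0 − f) = T1 − T0. The correction vanishes exactly.
- Linear in age, age updated by one year: f(age + 1) − f(age) is the same constant for everyone, so no correlation changes.
- Non-linear in age, age updated: the difference varies with age, so cancellation is partial.

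An illustrative simulation had 200,000 people with ages uniform from 65 to 85. Baseline score fell 0.4 points per year of age, and the change fell 0.1 points per year of age. Correlation of age with the cognitive measure:

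| Measure | Correlation with age |
|---|---|
| Raw change | −0.141 |
| Change, additive correction, fixed age | −0.141 |
| Change, linear correction, updated age | −0.141 |
| Change, divided by an age-specific SD | −0.141 |
| Change, quadratic correction, updated age | −0.084 |
| Level, raw | −0.27 |
| Level, corrected | about 0 |

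The correction works on levels. In none of the forms tried does it remove age from the change.

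**How much could age induce?** If age correlates a with volume change and b with cognitive change, and nothing else links them, the induced correlation is a × b. Rejection rates of a two-sided 5% Pearson test (40,000 simulated studies per row):

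| a = b (assumed) | Induced r | n = 56, unadjusted | n = 70, unadjusted | Age partialled out, n = 56 / n = 70 |
|---|---|---|---|---|
| 0.2 | 0.04 | 6.2% | 6.3% | 5.0% / 5.0% |
| 0.3 | 0.09 | 10.2% | 11.5% | 5.1% / 5.0% |
| 0.4 | 0.16 | 21.8% | 26.5% | 5.0% / 4.9% |
| 0.5 | 0.25 | 46.4% | 55.7% | 4.7% / 5.1% |

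The critical |r| is t / √(n − 2 + t²), which is 0.263 at n = 56 and 0.235 at n = 70. The induced r reaches it only if both age correlations are about √0.263 = 0.51, or √0.235 = 0.48.

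**Does matching help?** Matching makes the controls' age distribution resemble that of the surgical patients. It leaves the spread of age within the surgical group as it was, and that spread drives the induced correlation.

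**The case against.** The strongest reply is that the article condenses a fuller protocol and perhaps a separate analysis plan, where a covariate list for a secondary correlation would normally sit. That is fair: silence on covariates alone would be no finding, and an adjusted analysis may well be planned. What remains is that the article does fix the score and the correlation, and describes that correlation in two ways that do not agree.

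Several stronger readings are tempting, and the documents do not support them.

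- *The corrected score is the only demographic adjustment in the plan.* It is not: controls are matched on age, gender and education, and the POCD variables are normed. Neither acts on this correlation within the surgical group.
- *The plan presents the corrected score as control of confounding, or calls the secondary result age-adjusted.* It says only how cognition is quantified.
- *The correction cancels, full stop.* That needs an additive or linear form, which is in a source not shown. The quadratic case cancels only in part.
- *Age will produce the secondary result.* The documents give no age correlation with either change. At 0.2 on both sides the error rate is close to nominal. The cohort also excludes dementia, low MMSE and cerebral pathology, and follow-up is one year, so high correlations should not be presumed.
- *The corrected score must be replaced by the raw one.* If the two changes are equal, replacing it gains nothing.

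It is also true that this is a secondary endpoint in a study that describes itself as having pilot character.

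**Conclusion.** The point holds in a limited form. For the endpoint defined in Outcomes, the score's demographic correction cancels or nearly cancels if it is additive or linear in age, and matching does not fill the gap. A plain correlation would then leave age uncontrolled in a cohort aged 65 or older with no upper limit. The false-positive rate at n = 56 runs from about 6% to about 46% as the assumed age correlations go from 0.2 to 0.5. It is modest at the lower end and serious only when both correlations approach 0.5. These figures rest on equal age correlations on both sides, no other link between the changes, and normally distributed data.

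Separately, and without any assumption, Outcomes specifies changes while the Statistical analysis plan section can be read as levels, and the two should be aligned. This is worth correcting because the remedy is nearly free.

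**What to change.** In the Statistical analysis plan section, state that the secondary analysis relates change in volume to change in the CERAD-NAB total score, in agreement with Outcomes. Report it as a partial correlation, or the equivalent regression, adjusted for age, sex and education, with its confidence interval.

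Age, gender and education are already needed to match the controls, so no new data are required. With one term each, residual degrees of freedom at n = 56 go from 54 to 51. The demographically corrected score may be kept. Baseline regional volume and intracranial volume are optional sensitivity covariates: adjusting an observational change for its baseline is debatable, and the imaging section does not list intracranial volume.

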### Statistics

#### Sample size justification

Sample size is estimated based on data describing hippocampal volume. The clinically relevant difference is defined as the difference in hippocampal volume between normal subjects (2.8 ± 0.5 cm^3^) and patients with mild cognitive impairment (2.4 ± 0.4 cm^3^) [29]. Assuming an incidence of POCD of 41% one week after surgery in this age group [2], and a standard deviation of the hippocampal volume change of 0.45 in both patients with and without POCD, a total sample size of 56 subjects may detect a difference of 0.4 cm^3^ in hippocampal volume [29] with a power of 90% at a two-sided significance level of 5%. To compensate for the high loss to follow-up, which is unfortunately typical for studies on POCD [31] and estimated at 20%, we will recruit 70 patients in the surgical group (Group 1). The number of study participants in the nonsurgical control group (Group 2) is arbitrarily set at 30.

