#### Diagnosis of POCD

POCD is a complex neuropsychological disorder presenting as a decline in various cognitive domains after surgery and may at times be difficult to diagnose. Clinical cognitive outcomes research is complicated by the fact that there is no universal definition of POCD. Assessment for POCD comprises a time-intensive combination of neurocognitive function tests, and expert evaluation is mandatory for a valid diagnosis of POCD. In the literature, large differences in methodology (e.g., the test batteries used, the interval between sessions, the endpoints to be analyzed, statistical methods) and diagnostic criteria for POCD are apparent [31]. In our study, the diagnosis of POCD is based on a decrease of standard scores in the CERAD-NAB.

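### The POCD rule measures decline in between-person SD units, not retest-change units, and as written leaves out the 30 controls, so stable patients can enter the POCD group of the primary comparison

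*Protocol article*

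**What the plan says.** Under Neuropsychological assessment, the test variables "are converted into standard scores (z-scores) based on a normative sample" and changes from baseline are taken on that scale. The rule follows: "POCD is diagnosed if the decline is >1.0 standard scores in two or more of the 15 variables". It is tied to diagnostic guidelines for mild cognitive impairment and dementia. No retest SD, reliability or expected false-positive rate accompanies it.

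On practice effects, the same section says: "A correction for short-term practice effects will be carried out based on previous work". Choice of study collective, in the Discussion, says: "The addition of a group of nonsurgical participants serves to control for practice effects related to neuropsychological assessment". Sample size justification adds: "The number of study participants in the nonsurgical control group (Group 2) is arbitrarily set at 30".

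Under Outcomes, the primary endpoint is "the degree of change in hippocampal volume over time between patients with and patients without POCD". Diagnosis of POCD, also in the Discussion, remarks that "expert evaluation is mandatory for a valid diagnosis of POCD", but no adjudication step is attached to the rule.

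The rule counts 15 variables, whereas Table 3 lists 13.

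**The concern.** A normative SD describes the spread of scores across people at one sitting. Whether a drop of 1.0 on that scale is unusual for an unchanged person depends on retest reliability. When reliability is moderate, such drops are common on a single score, and requiring only two among 15 makes a chance diagnosis more likely still.

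The label is the grouping variable of the primary endpoint. Stable patients placed in the POCD group pull its mean hippocampal change towards that of the other group, which biases the difference towards zero and lowers power. The reported POCD incidence would also contain an unknown share of retest noise. The 30 matched controls could reveal that share, but the rule makes no use of them.

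**Working it through.** **1. The plan's own sample size.** Inputs from Sample size justification: difference 0.4 cm³, SD of change 0.45, 41% POCD, two-sided 5%, power 90%.

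Total N = (1.960 + 1.282)² × 0.45² / 0.4² / (0.41 × 0.59) = 54.98. For 56 patients split 23/33, power is 90.5% (normal) or 89.5% (noncentral t). Then 56 / 0.8 = 70. The stated figures reproduce.

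**2. Chance of a drop above 1.0 on one score.** The documents state no chance-positive rate, so there is none to reproduce. Assume no true change, mean practice gain fully removed, normal changes and the same retest reliability r for every score. Neither r nor the correlation between change scores (rho) is in the documents; both are assumptions shown over a range.

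SD of z-change = √(2(1 − r)); p = Φ(−1/SD).

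- r = 0.6: SD 0.894, p = 0.132
- r = 0.7: SD 0.775, p = 0.098
- r = 0.8: SD 0.632, p = 0.057
- r = 0.9: SD 0.447, p = 0.013

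**3. Chance of meeting the full rule.** For independent changes, P(at least 2 of m) = 1 − (1 − p)^m − m·p·(1 − p)^(m−1). At r = 0.7 and m = 15 this is 1 − 0.211 − 0.346 = 0.44. For rho above 0, a one-factor normal model was integrated numerically. Ranges below cover rho from 0 to 0.5.

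| r | 15 scores (rule) | 13 scores (Table 3) |
|---|---|---|
| 0.6 | 38–61% | 35–53% |
| 0.7 | 30–44% | 27–37% |
| 0.8 | 18–21% | 16–18% |
| 0.9 | 1.5–4% | 1–3% |

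**4. Effect on the primary comparison.** Let π be true incidence and f the false-positive rate, with full sensitivity. Labelled share = π + f(1 − π); PPV = π / labelled share; expected difference = 0.4 × PPV. Power uses the noncentral t at N = 56 with SD 0.45, ignoring the small rise in SD from mixing.

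At f = 0.20 and π = 0.41: labelled share = 0.41 + 0.20 × 0.59 = 0.528; PPV = 0.41 / 0.528 = 0.777; difference = 0.31 cm³.

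| π | f | PPV | Difference (cm³) | Power |
|---|---|---|---|---|
| 41% | 0 | 100% | 0.40 | 90% |
| 41% | 5% | 93% | 0.37 | 86% |
| 41% | 20% | 78% | 0.31 | 72% |
| 41% | 30% | 70% | 0.28 | 61% |
| 12.7% | 0 | 100% | 0.40 | 59% |
| 12.7% | 20% | 42% | 0.17 | 24% |
| 9.9% | 0 | 100% | 0.40 | 50% |
| 9.9% | 20% | 36% | 0.14 | 18% |

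The 12.7% and 9.9% rows use 3-month rates from Table 1; the first postoperative MRI is at 3 months. In those rows low incidence has already lowered power before any mislabelling.

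**The case against.** **Reliability is unknown.** The documents give neither r nor rho, and near r = 0.9 on every score the problem is minor. Some scores are bounded counts, and some derive from others (delayed recall and savings), so the independence end of each range is a ceiling rather than an expectation. This stands. A reader might infer that the rule has a very high chance-positive rate as a matter of fact; the documents do not support that as an unconditional statement.

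**Extreme scenarios mix two problems.** With 12.7% incidence, 90% sensitivity and a 30% false-positive rate, PPV is 30%, the difference is 0.11 cm³ and power is about 15%. A reader might conclude that most labelled POCD is noise and that mislabelling destroys the study. But at 12.7% with perfect labels power is already about 59%; that part of the loss belongs to the incidence assumption. At the planning incidence of 41%, most labelled cases remain true at false-positive rates of 20–30%.

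**Practice effects are addressed.** A correction is planned, and the Discussion gives the controls that role. A reader might infer that the controls are ignored throughout; that goes too far. A correction based on previous work may mean a published method rather than external values. What stands is that the two sections need reconciling. Correcting the mean in any case leaves random retest variation, and the rates above already assume no mean drift.

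**Expert evaluation could remove false positives.** It might, but it is not part of the written rule.

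**There is no universal POCD definition, the study describes itself as having pilot character, and the secondary endpoint correlates continuous changes.** All true, and the secondary endpoint does not depend on the label. The primary endpoint does.

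**Conclusion.** The concern holds in conditional form. The rule as fixed makes no allowance for the variability of change in stable people and does not use the controls available to measure it. For assumed reliabilities of 0.6 to 0.8 it would label roughly 18–61% of unchanged people as POCD with 15 scores, or 16–53% with 13. At 0.9 throughout, the rate is at most about 4%.

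At the protocol's own 41% incidence, false-positive rates of 20–30% would reduce the expected difference to 0.31–0.28 cm³ and power to about 72–61%. These figures rest on a common reliability across scores, normal changes, full sensitivity and an SD of 0.45.

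**What to change.** For each score and visit, compute (patient change − mean control change over the same interval) / SD of control change. Define POCD on that scale with a conventional cut-off fixed in advance. The chance-positive rate then no longer depends on an unknown r. As an illustration, with a cut-off of 1.96 on 2 of 15 independent scores, p = 0.025 and the rate is 1 − 0.975¹⁵ − 15 × 0.025 × 0.975¹⁴ = 1 − 0.684 − 0.263 = 5.3%; with rho up to 0.5 it is at most about 8%, ignoring error in the control SDs.

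Do not tune the cut-off so that 5% of the controls meet it. That would rest on one or two people; 1 of 30 has an exact 95% interval of 0.1–17%.

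Report the positive rate of both the new and the current rule in the controls with confidence intervals, and keep the current rule as a sensitivity analysis. Reconcile Neuropsychological assessment, Choice of study collective and Diagnosis of POCD on the source of the practice correction and the role of expert evaluation. Reconcile the 15 variables with the 13 in Table 3.

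Cost: mainly analysis wording, provided the controls are tested at the same intervals as the patients, which the text does not state. Control SDs are imprecise: the standard error is about 1/√(2n), or 13% for 30 controls and 14% for 24 (if 20% are lost). If reliability is below about 0.87, where 1.96 × √(2(1 − r)) equals 1.0, a 1.96 cut-off is stricter than the current one and fewer patients will be labelled POCD.
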